**At the assessment visits (Baseline and 6 months) participants will be required to complete the following assessments:**

- a) Mental health care: A list of current medications; medication history, including antipsychotic, antidepressant, mood stabilisers, non-psychiatric medications and non-prescription drugs and vitamin supplements will be gathered at each time point. We will establish the duration of untreated psychosis (DUP) at baseline using the Nottingham Onset Schedule (NOS). Use of key NHS services contact questionnaire will measure the total number of hospital admissions and the amount of contact with the home treatment team throughout the duration of the trial. This will be recorded from the time of consent up to the Month 6 assessment. Data will be collected from patients at their final assessment and checked against medical notes. For patients who are lost to follow-up, this data will be obtained from medical notes only.
- b) Biomedical / Cardiovascular status (secondary endpoint) will be measured at each time point as: waist circumference, weight, height (for BMI), blood pressure, heart rate (pulse) (Anthropometric measures), along with blood measures of cardiovascular risk / inflammatory markers and smoking habits. (Measures which form part of routine clinical care will be shared with the clinical team if the patient wishes).
- c) Mental health status (primary and secondary endpoints): the Positive and Negative Syndrome Scale (PANSS); Global Assessment of Functioning (GAF). The GAF will be rated first, from clinical notes at the time of first presentation to services for psychosis and then again at baseline to ensure an accurate representation of functioning at both the onset of illness and at the time of consent; Calgary Depression Scale (CDS); OPCRIT (Operational Criteria checklist) will be performed during the trial to ensure that we have a researcher-led clinical rating independent of the diagnosis retrieved from clinical notes at the time of screening.
- d) Urine pregnancy tests in females, monthly, at each treatment visit (If positive, IMP will be discontinued). In the event that it is not possible to obtain a urine sample, a blood HCG sample will be obtained and tested for pregnancy. No IMP will be administered without ascertaining pregnancy status. Pregnancy tests will not be done for female participants who are permanently sterile (e.g. who have undergone hysterectomy, bilateral salpingectomy or bilateral oophorectomy) or who are post-menopausal (no menses for 12 months without an alternative medical cause).
- e) Levels of sun exposure, including type of clothing worn, levels of physical activity (IPAQ) and SIMple Physical Activity Questionnaire (SIMPAQ), skin type (Fitzpatrick Skin Type questionnaire), vitamin D food frequency questionnaire (Other influences on Vitamin D levels).
- f) Adverse event assessment will be systematically addressed during the monthly contact with the participant. Additionally, at the 3 month visit a blood sample will be taken to monitor corrected serum calcium ( $\text{Ca}^{2+}$  levels or "bone screen"). A parathyroid hormone

test (PTH) will be performed on the same blood sample if  $\text{Ca}^{2+}$  is above normal range. If participants report nausea and vomiting between visits, they will be advised to contact their doctor for a  $\text{Ca}^{2+}$  blood test.

- g) At each dosing visit and during the follow-up phone call, participants will be asked whether they think they were assigned to receive the treatment (vitamin D) or the placebo, and their reason for this. This is to record how well the blind was maintained throughout the study

## 7.2 Laboratory Tests

All blood samples will be obtained by a trained phlebotomist.

Blood will be taken for 25OHD concentration at baseline and 6 months but this assay will not be performed until the trial is complete. This is to ensure that researchers and clinicians are blind to baseline vitamin D status and that the patients will be offered standard clinical treatment. Additionally there is clinical equipoise regarding vitamin D supplementation in this group (i.e. the uncertainty of the intervention's efficacy versus the potential that leaving participant's vitamin D deficient will cause harm). This strategy has been employed successfully by one of the investigators ([name]) elsewhere (Gaughran et al., 2007). At the end of the study, once all data is analysed we will inform the participant's respective clinical team and/or GP of their vitamin D levels at last testing, noting that it may be some time after that test. Appropriate recommendations for post-study vitamin supplementation will be made by patient's GP or clinical team. Once the study is complete, serum samples will be shipped to the funder (Stanley Medical Research Institute) as part of the funding agreement, in an anonymous format. The Biomedical Research Centre (BRC) will store this sample until it is ready to be shipped to America. Clinical markers for cardiometabolic and general health will be tested from the same bleed (and shared with the clinical team with the patient's permission), and samples stored to later test for immune/inflammatory markers. Safety tests include calcium and if indicated parathyroid hormone test.

### 7.2.1 DNA

From the blood samples collected at baseline, in patients who have additionally consented to genetic testing, we will also extract DNA, to explore possible interactions between common variants in vitamin D pathways and clinical outcomes (as been recently demonstrated in a study of vitamin D supplementation for Parkinson's Disease - Suzuki et al., 2013). Patients will also have the option to have their DNA stored in the NIHR BioResource Centre Maudsley and the NIHR BioResource. The biobanking and long-term storage of DNA will be described in the BioResource's PIS and subject to separate consent.

### 7.2.2 RNA

Patients consenting to the study at an early stage will be asked to give a blood sample for RNA. RNA analysis at baseline and 6 months will be used to explore gene expression after supplementation (Hosseini-nezhad, 2013). These blood samples will be collected at the same time as the baseline/Month 6 vitamin D samples, in separate blood tubes. The samples will be

delivered directly to the BRC Biobank at the SGDP (Social, Genetic and Developmental Psychiatry) building at King's College London.

Patients enrolling at a later stage and consenting to ICF v10 (dated 09.01.2019) will no longer be asked to provide RNA. Enough paired samples have been collected and the added burden to patients should be prevented.

## 8. Assessment of Efficacy

### 8.1 Efficacy Parameters

#### 8.1.1 Primary Efficacy Parameters

Difference between trial arms in Positive and Negative Syndrome Scale (PANSS) total score at 6 months in all FEP patients.

#### 8.1.2 Secondary Efficacy Parameters

The following measures will be assessed in all participants irrespective of vitamin D concentration:

- Positive and Negative Syndrome Scale (PANSS) at 3 months
- Positive and Negative Syndrome subscores (Positive Scale, Negative Scale and General Psychopathology Scale) at 3 and 6 months
- Global Assessment of Functioning (GAF) at 6 months
- Calgary Depression Scale at 6 months
- Cardiovascular risk markers (Waist circumference, BMI, HBA1c, Total Cholesterol & CRP) at 6 months

We will also measure the efficacy of vitamin D supplementation at 6 months as indicated by 25OHD blood concentration levels.

In addition to the whole sample, we will examine PANSS total scores at 3 and 6 months in a subsample of those with suboptimal baseline vitamin D levels.

#### 8.1.3 Exploratory moderator analysis

Inflammatory markers will be measured and examined as a tertiary/exploratory efficacy parameter. This will not form part of the primary or secondary analyses. These post-hoc analyses will only become clear once the main objectives of the trial have been evaluated. The trial population for which we wish to investigate these markers as potential predictor markers (predictors of treatment effects) can only be defined once the investigators have a clear summary of where vitamin D is effective, i.e. in the entire (non-tested) population or the vitamin D insufficient / sufficient population. Interaction with treatment effects can be used to evaluate these variables.

Serum aliquots will be sent to the funder, Stanley Medical Research Institute in the USA, for future inflammatory marker analysis.

## 8.2 Procedures for Assessing Efficacy Parameters

Concerning efficacy, psychopathology will be assessed with the PANSS total score and related sub-scores, Global Assessment of Function (GAF) and Calgary Depression Scale, and 25OHD blood concentration levels at 6 month assessment visits.

Blood will be taken for 25OHD concentration at baseline and 6 months but this assay will not be performed until the trial is complete.

Concerning follow-up, all participants will be seen by trained research staff each month for the administration of the intervention. Research staff will assess outcomes at baseline, 3 (PANSS only) and 6 months, including anthropometric/cardiovascular assessments. With prior consent from the participant clinically relevant measures will be shared with the clinical teams to minimise duplication of assessments.

Primary outcomes will be assessed at 6 months in order to reduce the influence of attrition. Based on past research undertaken in London, we expect that up to 20% of FEP will drop out by 6 months.

Concerning safety, at study entry, all patients will be assessed with a physical examination, including weight, blood pressure, and pulse rate. Bloods will be taken at baseline and 3 months, in order to assess serum calcium (corrected for serum albumin) and parathyroid hormone (PTH) where indicated and at additional times if there is evidence of symptoms of hypercalcaemia. Side effects will be systematically assessed at each month prior to administration of the intervention (IMP/placebo).

## 9. Assessment of Safety

### 9.1 Specification, Timing and Recording of Safety Parameters

Any adverse event that occurs between the time of consent to the study through to 28 days following their last dose will be recorded via a telephone conversation with the participant. Should a participant not receive the IMP dose during final assessment, for example if outside of the dosing window, a follow-up telephone call will not be needed. Should a participant withdraw from the trial, AEs will be recorded up to 28-days after their last dose. Every reasonable effort ~~Three attempts, approximately one week apart,~~ should be made to contact the participant for their 28-day post-last dose telephone call to record any AEs. The investigators will assess whether the adverse event may be related to the subject's participation in the study.

Particular attention will be paid to symptoms of hypercalcaemia which are: loss of appetite, nausea, vomiting, constipation, abdominal pain, increased thirst, frequent urination, fatigue, weakness, and muscle pain.

In addition, the following assessments will be used to determine subject safety during the study at baseline and 3 months:

1. Corrected serum calcium ( $\text{Ca}^{2+}$  levels or "bone screen"), will be performed at baseline, and three months and more frequently if nausea and/or vomiting occur.
2. A parathyroid hormone test (PTH) will be performed on the same blood sample if  $\text{Ca}^{2+}$  is above normal range. If participants report nausea and vomiting between visits, they will be advised to contact their doctor for a  $\text{Ca}^{2+}$  blood test.
3. A urine dipstick pregnancy test (beta-HCG) will be performed for all females at baseline. Female participants of child-bearing age refusing a pregnancy test at baseline will be excluded from participating in the trial. At each treatment visit (monthly for 6 months) a urine dipstick pregnancy test will be performed to determine pregnancy status. Pregnancy tests will not be done for female participants who are permanently sterile or who are post-menopausal (no menses for 12 months without an alternative medical cause). If the urine test is positive, the participant will be withdrawn from the trial medication but encouraged to remain in the study. At 3 and 6 month visits the researcher will perform a urine dipstick test to ascertain pregnancy status. In the event that it is not possible to obtain a urine sample, a blood HCG sample will be obtained and tested. No dose of IMP will be administered to female participants without first checking pregnancy status (except for patients who are permanently sterile or post-menopausal, as described above).

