### 5.6 Subject Compliance

Participants will be given IMP/Placebo orally by one of the research team with appropriate training and delegation to do so. The researcher will complete a source data worksheet to state the time, date, amount of IMP administered and the administering researcher for each dose administered throughout the study period.

As previously mentioned, the participants will be given the IMP/placebo once a month for 6 months. A dosing visit will be scheduled each month for a total of 6 months, where the initial dosing date, acts as the anchor date for all future visits (i.e. the first appointment should be scheduled a month after from the initial dose, and so on). A minimum of a 24-day interval between doses must be adhered to throughout the study to ensure that patients are not dosed too closely. A visit window of -2/+2 weeks from the anchor date will be set to allow room for missed/rescheduled appointments. If a dose is missed, the participant will be allowed to carry on with the trial and the next dose of treatment (either IMP/placebo) will be administered at the next scheduled time point; in such instances a protocol deviation will be logged.

We will seek permission from participants to voluntarily provide contact details of a close relative or friend plus at least 2 means of contact including email address, mobile phone number, landline phone number, in order to improve the likelihood of contacting patients at future follow-up points. We will note which is their preferred method. This information will be stored on a separate contact details form and will be kept in a locked file by the team administrator. We will make it explicitly clear that the contact details of a significant other will only be used in situations whereby we are unable to contact the participant in the first instance.

In the event that a participant decides they no longer wish to take the treatment (IMP/placebo) they will be encouraged to continue with the study, if agreeable they will be followed up at the main assessment points (6 months) but routine safety checks will not be offered, except for any due after their last dose of IMP and no drug will be administered. Participants are free to drop out from the study at any time.

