| Service Contacts Form                                                                                   | X                      |               |                                                                                               |               | X                                                          |                      |                   | X                     |

\* In the event that it is not possible to obtain a urine sample, a blood HCG sample will be obtained and tested for pregnancy. No IMP will be administered without first ascertaining pregnancy status. Pregnancy tests will not be done for female participants who are permanently sterile or who are post-menopausal (no menses for 12 months without an alternative medical cause).

\*\* AEs collected from consent. Patients will be phoned 28 days post the last dose of treatment at 6 months to check for any adverse events. At dosing visits 1 – 6, we will assess adverse events in person with the participant at their scheduled visit. If no IMP is given at the Month 6 visit, no follow-up call will be needed. Should a participant withdraw from the study, AEs will need to be collected up to 28 days after their last dose.

\*\*\* Blood sampling for calcium levels (including parathyroid hormone test) will only be performed at these time points if patient reports nausea and vomiting.

\*\*\*\* The IMP is administered once a month, every month for 6 months.

\*\*\*\*\* The 9-month safety check and 12-month assessments will only be performed on those patients who have received more than 6 monthly doses of the IMP prior to the protocol change dated (02.06.17). However, the IMP/placebo will no longer be administered after 6 months.

DFEND Protocol Version 10.1 03.05.2019

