### **9.2.1 Adverse events that do not require reporting**

All SAEs will be reported for this trial except hospitalisations due to deterioration in mental state, as we anticipate a high proportion of our participants will be hospitalised for this reason during the trial.

The period for AE reporting is from consent to 28 days post last IMP administration. All AEs will be reported.

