### 9.3 Treatment Stopping Rules

The trial may be prematurely discontinued by the Sponsor, Chief Investigator or Regulatory Authority on the basis of new safety information or for other reasons given by the Data Monitoring Committee, Trial Steering Committee, regulatory authority or ethics committee concerned.

If the trial is prematurely discontinued, active participants will be informed and no further participant data will be collected. The Competent Authority and Research Ethics Committee will be informed within 15 days of the early termination of the trial.

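### The Month 6 call waiver ignores time since the last dose, so it conflicts with the 28-day adverse-event period for participants assessed less than 28 days after dosing

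*Combined protocol and SAP*

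**What the plan says.** Protocol 9.1 sets the AE period: "Any adverse event that occurs between the time of consent to the study through to 28 days following their last dose will be recorded". Protocol 9.2.1 restates it without exception: "The period for AE reporting is from consent to 28 days post last IMP administration. All AEs will be reported". For people who leave, 9.1 keeps the same length: "Should a participant withdraw from the trial, AEs will be recorded up to 28-days after their last dose".

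The waiver is also in 9.1: when the participant is not dosed at the final assessment, "for example if outside of the dosing window, a follow-up telephone call will not be needed". The Table 1 footnote marked ** in 7.1 agrees: "If no IMP is given at the Month 6 visit, no follow-up call will be needed". Neither mentions time since the last dose.

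Protocol 6.6 (repeated in SAP 1.4) keeps each participant on trial until the post-6-month call and ends the trial at the last patient's call.

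Protocol 5.6 gives the timing rules: dosing visits within 2 weeks either side of schedule, the Month 6 assessment from 4 weeks before to 6 weeks after, and "A minimum of a 24-day interval between doses must be adhered to throughout the study".

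On premature discontinuation, 9.3 states that "active participants will be informed and no further participant data will be collected".

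**The concern.** The waiver makes sense if a participant not dosed at Month 6 was last dosed a month or more earlier, because the 28 days are then over and AEs are taken at the visit itself. The text does not require that. The assessment window opens two weeks before the dosing window, so an undosed Month 6 visit can fall soon after a dose while remaining within the assessment window. No later contact is scheduled for such a participant, since the 9- and 12-month visits apply only to a legacy group.

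Two things are at stake. First, a completer seen early has a shorter period of active AE questioning than a participant who withdraws, and no reason is given. Second, the safety section of SAP 3.1.2 tabulates AEs by time, phase and arm with the number still in the trial at each time point. It does not say how participants with a shortened final period are counted.

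**Working it through.** The plan states no figure to reproduce; this is date arithmetic on its own windows.

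**Inputs**
- AE period: 28 days after the last dose (Protocol 9.1, 9.2.1).
- Month 6 assessment offset *a*: −28 to +42 days (Protocol 5.6; SAP 1.6).
- Preceding dose offset *d*: −14 to +14 days (Protocol 5.6).
- Minimum interval between doses: 24 days (Protocol 5.6).
- Assumptions: one month is 30.4 days; the last dose was at the preceding monthly visit; the two-week dosing window also applies at Month 6; no separate dosing visit follows the assessment.

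**Formulas**
- Gap = 30.4 + *a* − *d*
- Days without a scheduled AE contact = max(0, 28 − gap)

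**Results** (combinations with a gap under 1 day are left out)

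| Month 6 visit, *a* | Preceding dose, *d* | Gap (days) | Days uncovered |
|---|---|---|---|
| 0 | 0 | 30.4 | 0 |
| +15 to +42 | −14 to +14 | 31.4 to 86.4 | 0 |
| −28 to −15 | −14 | 16.4 to 29.4 | 0 to 11.6 |
| −28 to −15 | −7 | 9.4 to 22.4 | 5.6 to 18.6 |
| −28 to −15 | 0 | 2.4 to 15.4 | 12.6 to 25.6 |
| −28 to −15 | +7 | 1.4 to 8.4 | 19.6 to 26.6 |
| −28 to −15 | +14 | 1.4 | 26.6 |
| −14 to −7 | 0 | 16.4 to 23.4 | 4.6 to 11.6 |
| 0 | +14 | 16.4 | 11.6 |

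The five rows with *a* from −28 to −15 are visits too early for the dosing window, which is the kind of reason 9.1 gives for not dosing. The last two rows lie inside the dosing window, but a dose due at that visit would be barred because the gap is under 24 days.

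For the 24-day mechanism alone, gaps of 1 to 23 days leave 28 − 23 = 5 to 28 − 1 = 27 days uncovered. Visits before the dosing window can also produce gaps of 24 to 27 days, which leave 4 to 1 days uncovered.

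The protocol does not settle whether a dose is due at Month 6. Six monthly doses starting at month 0 would end at month 5, while Table 1 marks administration at the 6-month visit and its footnote refers to a last dose at 6 months. The gap from the preceding monthly dose is the same on either reading. On the first reading the call is waived because no dose is due, and the 24-day rule plays no part.

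**The case against.** The strongest reply is that little is lost in practice. An on-schedule participant is seen about 30 days after the preceding dose, and a visit more than two weeks late comes at least 31 days after it. Table 1 provides for AE recording and a calcium sample at the 6-month visit. Only a scheduled call is waived: 9.2.1 still requires AEs to be reported to day 28, and 5.3 tells patients with hypercalcaemia symptoms to contact their GP, who is to report hypercalcaemia to the coordinating centre. All of this stands and limits the point to loss of active questioning in a subset of unknown size. It does not remove the contradiction.

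Three stronger readings are tempting, and the documents do not support them:
- **Every safety call disappears, so AEs are lost trial-wide.** If doses run from months 0 to 5, the waiver would reach everyone, but on-schedule participants would still lose no AE days. Table 1 also marks a dose at Month 6.
- **The between-arm comparison is biased.** Participants and site staff are blind, and nothing suggests that early visits or late doses differ by arm. The harm is incomplete capture.
- **The missed days are when hypercalcaemia would show itself.** No section says when symptoms would appear.

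The end-of-trial definition is also only partly affected. The trial's end date rests on the last patient's call; what fails generally is the statement that each participant stays until a call.

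**Conclusion.** The contradiction is in the current text and should be corrected. Applied literally, the waiver in 9.1 and the Table 1 footnote leaves some participants without a scheduled AE contact for part of the period that 9.1 and 9.2.1 require, and it cannot be squared with 6.6.

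The size is bounded. Only participants assessed less than 28 days after their last dose are affected. With the preceding dose on time and the visit too early for dosing, about 13 to 26 of the 28 days are uncovered; at the extreme, about 27. The wording conflict needs no assumptions. The day counts rest on a 30.4-day month, the preceding monthly dose having been given, and no dosing visit after the assessment. If the preceding dose was missed, the gap lengthens and the loss shrinks or vanishes.

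The early-stopping sentence in 9.3 is a separate inconsistency with a different trigger. Read literally, it ends AE collection for anyone dosed within the previous 28 days, against 9.1 and 9.2.1. It adds nothing to the size of the Month 6 problem.

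**What to change.** - In Protocol 9.1 and the Table 1 footnote marked **, make the waiver depend on time since the last dose: no call is needed only if AEs were assessed in person at least 28 days after the last dose; otherwise the 28-day call is made. Days without a scheduled contact then fall to zero by construction.
- In Protocol 6.6, with SAP 1.4 to match, let participation end at the 28-day call or, where the call is validly waived, at the Month 6 visit.
- Separately, reconcile 9.3 with the 28-day AE period for participants already dosed if the trial stops early.
- While editing, reconcile the passages on whether a dose is due at Month 6, so that it is clear when the call applies.

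The cost is a minor amendment and one telephone call by existing staff for each affected participant. No dose, visit window or analysis changes.

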For the follow-up assessment at 6 months a target visit window of -4/+6 weeks will be set to ensure follow-up data is collected. If the data can only be collected outside of this target visit window, it should be done anyway. For routine safety blood visits a -2 week window will be adhered to but an upper time frame will not be specified for collecting the safety bloods as these must be performed. Data collection will end at end of study defined in section 6.6.

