## 6.6 Expected Duration of Trial

The end of the trial will be defined as the last patient's post 6 month visit telephone call. Each participant will remain on the trial until they have each completed the post 6-month visit telephone call. The study will run from December 2015 until December 2019 to ensure that each participant has 6 months of exposure to either the active or placebo treatment.

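### The waiver of the 28-day safety call depends on whether a dose was given at Month 6, not on time since the last dose, so some undosed participants have no planned adverse-event contact to day 28

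*Combined protocol and SAP*

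**What the plan says.** **AE period.** Protocol 9.1: "Any adverse event that occurs between the time of consent to the study through to 28 days following their last dose will be recorded", by telephone. Protocol 9.2.1 agrees: "The period for AE reporting is from consent to 28 days post last IMP administration".

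**Waiver.** Section 9.1 removes the call for a participant who gets no dose at the final assessment, and a mistimed visit is only its example: "if outside of the dosing window, a follow-up telephone call will not be needed". The double-asterisk footnote to Table 1 (section 7.1) has no example and no condition: "If no IMP is given at the Month 6 visit, no follow-up call will be needed". The same footnote keeps the call for participants who are dosed at Month 6.

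**Withdrawals.** Section 9.1 keeps the full period for them: "Should a participant withdraw from the trial, AEs will be recorded up to 28-days after their last dose".

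**End of participation.** Section 6.6: "Each participant will remain on the trial until they have each completed the post 6-month visit telephone call". It defines the end of the trial by the last patient's call, and SAP 1.4 repeats both statements. Neither mentions waived calls.

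**Timing rules.** Section 5.6 allows dosing visits two weeks either side of target, with a floor: "A minimum of a 24-day interval between doses must be adhered to throughout the study". For the Month 6 assessment, "a target visit window of -4/+6 weeks will be set to ensure follow-up data is collected". Table 1 marks in-person AE recording at that visit.

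**The concern.** The waiver is harmless only if an undosed Month 6 visit always falls 28 days or more after the last dose, so that the in-person AE check closes the period. The protocol's own windows do not guarantee this. The 24-day minimum works the wrong way: a participant dosed too recently to be dosed again is, for that reason, also not called.

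The result is that some participants who stay in the trial and attend are followed for less time than participants who withdraw. No reason is given.

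What is at stake is planned safety contact after the final dose. Section 9.1 asks for particular attention to symptoms of hypercalcaemia, and the SAP (2.6, and the safety part of 3.1.2) summarises and compares AEs by arm. For a participant whose call is waived, the end of participation in 6.6 is also undefined.

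**Working it through.** The plan states no figure to reproduce. The check is date arithmetic on its own windows.

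**Inputs.** AE period 28 days (9.1, 9.2.1). Dosing window ±14 days, minimum interval 24 days, Month 6 window -28/+42 days (5.6). AEs recorded in person at Month 6 (Table 1). *Assumptions:* the last dose before Month 6 is due one month earlier, whatever its number, and a month is 30 days in the examples (28 to 31 days was also tried).

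**Formulas.** Interval = Month 6 visit day − last dose day. Uncovered days = max(0, 28 − interval).

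**Cases** (dose target day 150, Month 6 target day 180):

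| Situation | Interval (days) | Uncovered (days) |
|---|---|---|
| Both on target | 180 − 150 = 30 | 0 |
| Late edge of dosing window or later, previous dose 14 days late | at least 194 − 164 = 30 | 0 |
| Refused under the 24-day minimum | at most 23 | at least 28 − 23 = 5 |
| Previous dose 14 days late, Month 6 on target | 180 − 164 = 16 | 12 |
| Previous dose on target, Month 6 two weeks early | 166 − 150 = 16 | 12 |
| Previous dose on target, Month 6 four weeks early | 152 − 150 = 2 | 26 |

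With month lengths of 28 to 31 days, the first two rows stay at 28 days or more. On the early side (-4 to -2 weeks), 97% to 99.7% of possible day pairs are under 28 days.

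**How many could be affected.** The documents give no attendance data, so this is window geometry under an assumption and not a forecast. Take independent, uniform attendance and a 30.44-day month.

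- *Both visits within ±w days of target.* Here undosed and under 28 days means barred by the 24-day minimum. P(interval < 24) = (2w − 6.44)² / (2 × (2w)²), or 0 if 2w ≤ 6.44.
  - w = 14: 21.56² / 1568 = 0.30
  - w = 7: 7.56² / 392 = 0.15
  - w = 5: 3.56² / 200 = 0.06
  - w = 3: 0
- *Month 6 over the full -28/+42 days.* Visits within ±14 days have weight 28/70 = 0.4 and contribute 0.4 × 0.296 = 0.119. Early visits have weight 14/70 = 0.2. Of their pairs, 11.56²/2 ÷ 392 = 0.170 would put the visit before the dose and are not counted, and 2.44²/2 ÷ 392 = 0.008 are at 28 days or more. That leaves 0.822, contributing 0.2 × 0.822 = 0.164. Late visits contribute 0. Total 0.28.

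Month length matters. With a 28-day month, 6.44 becomes 4 and the ±7-day figure rises to 10²/392 = 0.26, and the ±3-day figure to 2²/72 = 0.06.

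**The case against.** Much can be said for the plan. The 28-day period is not shortened; what is lost is a scheduled contact. The waiver works in section 9.1's own example when the visit is late, and it works on schedule. Section 5.3 tells participants the symptoms of hypercalcaemia and sends them to their GP, who is to report hypercalcaemia to the coordinating centre. Calcium is sampled at Month 6. Sites that book visits to meet the 24-day minimum would create few of these cases. All of this stands, and it limits the size of the problem. It does not give the affected participants a planned contact to day 28, and it does not reconcile 6.6 with the waiver.

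Four stronger readings are tempting, and the documents do not support them:

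- *The call is taken from the most recently dosed.* Those dosed at Month 6 are the most recent, and they keep it. The group affected is the most recently dosed among those not dosed at Month 6.
- *Everyone with an interval under 28 days is affected* (33% over the full window, 42% within ±14 days, under the same uniform assumption). These shares include participants 24 to 28 days after a dose and inside the dosing window, who may be dosed and then called.
- *The by-arm tables treat these participants as fully followed, so the count is too low.* Nothing says so. SAP 3.1.2 has each table show how many were still in the trial at each time point. An undercount is possible but not shown.
- *The comparison between arms is biased.* Allocation is blinded and the rule is the same in both arms.

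**Conclusion.** The point holds as a conflict between the plan's own rules that should be corrected. Sections 9.1, 9.2.1 and 6.6 and the Table 1 footnote cannot all be followed for a participant not dosed at Month 6 whose last dose was under 28 days earlier. The gap is certain, at 5 days or more, for anyone refused under the 24-day minimum. It arises for nearly all visits on the early side of the Month 6 window.

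The per-participant loss follows from the documents' windows, given a monthly schedule. The share of participants does not: 28-30% rests on uniform attendance across the windows, and 0-15% on visits within 3 to 7 days of target with a 30.44-day month. Neither should be read as an expected count.

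One ambiguity bears on this. Table 1 lists dosing visits 1 to 6 with visit 1 as the anchor, which ends dosing at Month 5, yet also marks study drug at Month 6. If no dose is due at Month 6, the waiver would cover everyone who followed the schedule, and the 33% and 42% shares would then apply.

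**What to change.** 1. In protocol 9.1 and the Table 1 footnote, waive the call only if the Month 6 visit is at least 28 days after the last dose and AEs were recorded at that visit. Otherwise make the call at day 28 after the last dose. No participant then has uncovered days, provided the call is completed.
2. In protocol 6.6 and SAP 1.4, define participant completion and end of trial as the later of the Month 6 visit and any required 28-day call.
3. Reconcile the listing of dosing visits 1 to 6 with the study-drug mark at Month 6, in Table 1 and in the SAP schedule. Which is intended is for the trial team to state.

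The cost is a few sentences in an amendment and one extra phone call for some participants. No dose, interval or treatment rule changes.
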